## Abstract

**Background:**

Patients on dialysis are physically inactive, with most reporting activity levels below the fifth percentile of healthy age-matched groups. Several small studies have reported efficacy of diverse exercise interventions among persons with CKD and those on dialysis. However, no single intervention has been widely adopted in real-world practice, despite a clear need in this vulnerable population with high rates of mortality, frailty, and skilled nursing hospitalizations.

**Methods/design:**

We describe a pragmatic clinical trial for an exercise intervention among patients transitioning to dialysis. We will use an existing framework – Exercise is Medicine (EIM) – developed by the American College of Sports Medicine. After undertaking formative qualitative research to tailor the EIM framework to the advanced CKD population (eGFR < 30 ml/min/1.73m^2^), we will randomize 96 patients from two regions—Atlanta and Bay Area—in two intervention arms with incremental levels of clinical-community integration: physical activity assessment during Nephrology clinical visit, brief counseling at pre-dialysis education, and physical activity wearable (group 1) versus group 1 intervention components plus a referral to a free, EIM practitioner-led group exercise program over 16 weeks (group 2; 8 week core intervention; 8-week follow up). We will assess efficacy by comparing between group differences in minutes/week of objectively measured moderate intensity physical activity. To evaluate implementation, we will use questionnaires for assessing barriers to referral, participation and retention along the path of the intervention. Further we will have a plan for dissemination of the intervention by partnering with relevant stakeholders.

**Discussion:**

The overall goal is to inform the development of a practical, cost-conscious intervention “package” that addresses barriers and challenges to physical activity commonly faced by patients with advanced CKD and can be disseminated amongst interested practices.

**Trial registration:**

ClinicalTrials.gov identifier (Dated:10/17/2017): NCT03311763.

## Background

In 2017, 30 million adults or 15% of the United States population were estimated to have chronic kidney disease (CKD) [1]. It is well reported that minorities [2] have a higher reported incidence of CKD and end stage renal disease (ESRD), with African Americans and Hispanics having 3.9 and 1.5 (respectively) higher odds to develop ESRD compared to whites [3, 4]. Despite medical advances, CKD remains a debilitating disease with a myriad of understudied symptoms and consequences, including insomnia [5], depression [6, 7], low muscle mass [8, 9], and low physical activity (PA) levels [10–13], all contributing to substantial decrements in quality of life and adverse medical outcomes [7]. Nearly 95% of persons newly starting dialysis have physical fitness levels below the 20th percentile for the general population, and only 56.4% are reportedly able to walk one block [11]. Functional decline only accelerates after start of dialysis and leads to a negative spiral of deconditioning [14].

Prospective studies on patients with CKD requiring dialysis have shown a 60% or higher risk for mortality among those with the lowest level of PA compared to those with average or above average activity and/or fitness levels [13, 15, 16]. Further, sedentary behavior is associated with an increased risk for mortality among dialysis patients similar in magnitude to that of other well-established risk factors, such as a one-point reduction in serum albumin concentration [13]. Given the high cardiovascular mortality in persons with advanced CKD [17, 18] and the limited treatments available to patients who progress to end-stage kidney disease, there is a need to focus on promoting PA, a modifiable risk factor with potential for huge improvements in cardiovascular mortality, quality of life, and symptoms of uremia, which may improve tolerance dyalisis while countering the natural history of accelerated functional decline typically experienced by these patients [19]. The 12 month period preceding the anticipated start of dialysis may therefore be an important window of opportunity to implement PA interventions in this clinical population.

Previous intervention studies in persons with advanced CKD or those on dialysis have shown improvement in physical performance [20, 21], health-related quality of life [21–23], and muscle strength or quality [20, 24, 25] with exercise therapy. Additional studies provide evidence for anti-inflammatory effects of exercise training among persons with advanced CKD [26]. The interventions described in these studies have differed in many aspects: setting (in dialysis center versus home based), intensity (prescribed versus patient driven), and type (aerobic, resistance, or combined) [27]. Despite these efforts, no single intervention design has emerged as a sustainable standard of care model for nephrology practices interested in implementing standardized PA programming as part of CKD management.

For the present study, we plan an exercise intervention that optimizes use of existing resources to integrate PA in the management of patients with advanced CKD transitioning to dialysis, with the main purpose of creating a transferrable intervention “package” that acknowledges and tackles implementation barriers in clinical and community settings. For this, we adapted the Exercise is Medicine (EIM) Framework, an initiative conceived in 2007 by the American College of Sports Medicine (ACSM) and co-launched by the American Medical Association, with the ultimate mission of implementing evidence-based PA intervention as standard of care for every patient [28]. This includes approaches for routinely integrating PA assessment, counseling and prescription/referral programs, particularly for patients with chronic diseases [29]. Herein, we describe a protocol to adapt the EIM framework for integrating PA promotion among patients transitioning to dialysis, integrating in-depth interviews with patients with CKD and feedback from community partners and directly test, in a pragmatic trial, the feasibility and short-term impact of this intervention on PA levels and secondary outcomes.

## Methods

### Research rationale and objectives

The overall goal of this research is to develop and validate a pragmatic and scalable intervention, working with patients and community partners to adopt the existing EIM framework to improve PA levels among patients with advanced CKD but not yet in dyalisis (Fig. 1). We have three main objectives:Develop a framework for a PA intervention, seeking input from patients using a qualitative methodologySynthesize and use the findings from Aim 1 to implement a PA intervention and test it in a randomized controlled pragmatic trial (8-week intervention and 8 week follo-up periods) in two settings enriched with minority populations.In addition to assessing short term effectiveness of the intervention, focus on implementation by assessing the barriers to referral, participation, and retention along the path of the planned intervention and on future scalability by engaging relevant stakeholders.

**Fig. 1 Fig1:**
[figure not shown]
Study design. Questionnaires: Demographics, age, sex, race, ethnicity, education, if employed/actively working, cause of CKD, vascular access yes/no, other comorbidities, medications; Symptoms of Depression (CEDS-20), SF-12, Physical activity self-efficacy questionnaires; *CKD* Chronic Kidney Disease, *PA* Physical activity’

### Exercise is medicine framework

The EIM Framework serves as the backbone for this study (www.exerciseismedicine.org) https://www.quantextual.co/researcher/. This framework calls for routine assessment of PA during clinical interactions (called the “physical activity vital sign”), brief PA counseling, and a specific written PA prescription and/or referral to a community-based PA program, professional or resource. The PA prescription is often supplemented with referral to certified EIM practitioners (i.e. fitness professionals) that can lead exercise sessions, often group-based, tailored to specific chronic diseases. A feedback mechanism from the EIM practitioner to both the patient and to the physician is also recommended, often using PA wearable monitoring technologies [30]. An evaluation framework for EIM implementation in health care settings has also been published [31].

### Participant recruitment

The study design and inclusion/ exclusion criteria are shown in Table 1. English-speaking not yet on dialysis patients been seen at the two mentioned study clinical sites will complete a screening PA vital sign questionnaire, and thereafter study research coordinators will assess him or her for eligibility based on pre-specified inclusion/ exclusion criteria. Additionally, nurse recommendations and fliers briefly outlining the study posted within the kidney clinics will be used to help identify prospective participants. Potentially eligible patients will be contacted face-to-face or via telephone by a member of the research team to provide additional details on the study and its objectives. If ongoing interest is expressed, we will seek approval from nephrologists prior to enrolling. Research coordinators will obtain written consent from patients willing to participate in the trial.

**Table 1 Tab1:** Inclusion and exclusion criteria

Inclusion criteria • Not yet on dialysis, but eGFR < 30 ml/min/1.73m^2^ • Age ≥ 30 and ≤ 80 years • Self-reported Physical activity < 30 min/week of moderate intensity physical activity • Non-wheelchair bound • Able to provide informed consent in English • Anticipated to be living in the study area during the study period Interested in becoming more physically active over the next 6 months Exclusion Criteria • Inability to provide consent in English • Diagnosed mental health disorder • Alcohol or drug abuse • No fixed address or contact details • Unstable angina or unstable arrhythmias • Lack of access to internet • Any concern not otherwise stated by patient’s nephrologist	

### Formative data collection and intervention development

For the tailoring of the EIM framework for patients with advanced CKD, we will use (1) feedback from community partners and (2) in-depth interviews with patients with CKD at the intervention site. We aim to interview a total of 20 participants (10 per site), stratified by sex (male/female) and diabetes status (yes/NO) for a total of five patients in each sex-diabetes status strata. Participants will be asked to participate in a 1-h, semi-structured interview to discuss their exercise views and experiences, impact of CKD in exercise behaviors, opinions on planned intervention components (e.g., exercise classes, group-based exercise, mobile phone applications), and measures of programmatic success. Interviews will be digitally recorded using a smart phone equipped with specialized applications (Pocket Dictate for iPhone and Express Dictate for Andriod). Audiofiles will be transcribed verbatim for analysis. Transcripts will be reviewed and iterative processes will be employed to update the interview guide to add additional probes to gather more information or update questions if saturation is reached on a particular issue. An initial codebook including both deductive and inductive codes will be developed after reviewing all of the transcripts, and this codebook will be finalized through consultation with the study investigators. We will then conduct a thematic analysis, using MaxQDA (Verbi software) to assist with data manipulation and with structured comparisons of the data (men vs. women, individuals with and without diabetes, participants at each site) around key themes, to describe exercise behaviors and program recommendations from potential program users. The results of the analysis will then be applied to the EIM framework to finalize the intervention design.

### Baseline data collection

Data collection will occur at baseline and at 8- (V1) and 16 weeks (V2) after the interventions (Table 2). Personal information, including relevant medical history will be collected prior to the initiation of testing or intervention upon receiving participant consent. This will include patient characteristics of age, sex, basic anthropometric measures (height, weight, BMI and waist circumference), relevant comorbidities and medications.

**Table 2 Tab2:** Interventions examples

Class format	Minutes	Teachable moments
a. Strong bones and healthy hearts		
Warm-up and rhythmic stretch	10–12	• Pre-Warm-Up: Perceived exertion, breathing and hydration. • Action Planning: ROM safety through major/minor joints. • Warm-up: Large to small muscles.
Circuit Choreography	15	• Selecting the right tubing resistance, benefits of strength work, benefits of cardio work & the plus for both in a circuit format. • Resistance tubing safety. • Breathing techniques for strength work. • Cardio-cognitive benefits • Benefits of tempo changes through half-time, at music tempo and double- time tempos. • Benefits of non-dominant side movements.
Cool-Down	5	• Benefits of lowering the heart rate progressively.
Core Strengthening	5	• Benefits of concentric, eccentric strength training.
Flexibility Training	5–8	• Option - Chair transfer technique from chair to floor and from floor to chair. • Range of Motion versus Range of Movement.
Relaxation & Future Action Planning	5–10	• Breaking the symptom cycle and self-managing pain, fatigue, frustration, etc.
b. Stability & Balance for Fall Prevention		
Warm-up and rhythmic stretch		• Pre-Warm-Up: Perceived exertion, breathing and hydration. • Action Planning: ROM safety through major/minor joints. • Warm-up: Large to small muscles.
Core stability and strength training	5	• The muscle groups which compose the core. • Benefits of breathing for increasing abdominal chest wall strength and flexibility
Balance training	5–10	• Agility – changing center of gravity • Lower body strength
Stability training	5–10	• Stability in an unstable environment • How to protect the lower back during extensions • PNF stretching principles
Flexibility	10	• Stretch tight muscles for better posture • Use breathing to deepen stretches
Relaxation and Action planning	10	• Breaking the symptom cycle to better self-manage pain, fatigue, fear, anger, frustration and physical instabilities

### Randomization

Participants will be randomized to group 1 (low intensity) and group 2 (full –scale) intervention groups. Randomization will be conducted at a participant level prior to baseline testing by blocks of 16 via a computer-generated random number sequence by an independent researcher. Blinding of intervention group to clinical staff and participants will not be possible once the intervention starts.

## Trial interventions

### Group 1 and 2

#### Brief physical activity counseling

After study enrollment and assessment of the PA vital sign, a 30-min PA counseling session will be provided by the EIM – fitness professional. Evidence suggests that interventions should address individual, social and environmental factors to improve the likelihood of influencing behavior [32, 33]. Socio-ecological models of PA conceptualize and address the interaction and interdependency between individual, social and environmental factors [34, 35] and help identify the different environments where PA can be promoted, [36]. Health care and community settings are places where large proportions of the population can be reached and where PA can be effectively promoted [37–41]. By addressing multi-level influences for PA, the EIM intervention is rooted on socio-ecological approaches to increase the impact and sustainability of the intervention [33].

The PA counseling session will use brief-action planning, a highly structured, self-management support technique grounded in motivational Interviewing and behavior change strategies (goal setting, identify preferences and barriers, problem solving, stages of change and self-monitoring). Patients will be encouraged to incorporate moderate PA throughout the week to achieve 100–150 min/weekly, primarily through walking for leisure and transportation or other preferred activities [42].

#### Werable physical activity monitor

In order to support behavior change, all participants will receive a consumer-oriented “wearable” an associated smart-phone app to enable continued monitoring of y sustained by study participants as part of the study’s PA intervention programming (Fig. 2). The Garmin Vivofit 3 PA monitor was selected based on device usability and provision of evidence-based behavior change techniques, as summarized by a systematic content analysis of behavior change strategies implemented in commercially available electronic activity monitors https://www.quantextual.co/researcher/, [43]. The Garmin Vivofit 3 measures and displays steps, calories, distance, minutes of activity intensity and sleep time. Furthermore, the wearable device links to a health IT HIPAA-certified platform (Quantextual Inc) https://www.quantextual.co/researcher/. that automatically syncs the user’s PA information and allows them to self-monitor their progress, evaluate goals, interact with EIM study staff and share results with fitness professionals and providers on a free custom smartphone application (IOS or Android). This App will also enable the study staff to remotely monitor participants PA engagement. As such, the wearable device can be considered a component of the intervention in addition to providing process data.

**Fig. 2 Fig2:**
[figure not shown]
Integration of Exercise is Medicine framework into Quantextual Smartphone Application

### Group 2

#### Group-based physical activity program

*In addition to the intervention components previously listed, group 2 participants will also be referred to group-based PA program.* We will procure an exercise space at each study site that is close to Nephrology Clinics and convenient for most participants to hold group-based exercise sessions. Before implementation, EIM fitness professionals will participate in a single 6-h training session conducted by one of the authors of the curriculum. The training consisted of an introduction and discussion of the curriculum objectives, demonstration of activities, and overview of the program’s “Move and learn” activities.

At each location, we will make available blood pressure cuffs, glucometers and glucose strips for persons who experience symptoms related to hypotension or hypoglycemia during the class. Program sessions (8 persons per group) will be specifically designed for persons with CKD. Sessions will offer progressive aerobic conditioning, muscular strength and endurance, flexibility, and stability, balance and will be led by certified EIM fitness professionals [44].

Fitness professionals will follow the 2008 PA guidelines safety recommendations for PA programming tailored to persons with CKD and will be trained on communication skills and behavioral techniques (goal-setting, action planning, self-monitoring, provide instruction, feedback on performance, opportunities for social comparison, peer modeling, and social support) [45]. Two sessions/week will be offered, slowly progressing towards 50 min of light-to-moderate PA per session. Persons will also be encouraged to accumulate additional minutes of moderate PA throughout the week, primarily through increased walking for leisure and transportation. Interventions are structured around “*Move and Learn*” formats. They will include health education, led PA and lifestyle behavior change segments modeled after evidence-based sources (interventions examples are shown in Table 3) [46]. The social dynamics of the group will be used to forge strong, sustainable relationships with participants and reach appropriate minutes per week of PA, collect data using Health IT resources and provide guidance at the end of 8-week core intervention for transitioning to maintenance and self-managed PA. We will continue to offer the intervention even if the the participant initiates dialysis. For particiapnts who recently underwent surgery for dialysis access, we will encourage participation but limit arm exercise.

**Table 3 Tab3:** Study Procedures and measurements

	Baseline	Follow-up: 1	Follow-up: 2
		8 weeks	16 weeks
Self-reported			
Physical activity vital sign	√		
Medical history (or any changes thereof)	√	√	√
Quality of life (SF-12)	√	√	√
Qualitative Interview^a^	√		
Adverse events		√^b^	√
MEASUREMENTS			
Grip strength	√	√	√
6-min walk test	√	√	√
Anthropometry (measured BMI, waist circumference)	√	√	√
Blood pressure and blood glucose level	√	√	√
Weekly physical activity as measured by Garmin PA monitor	√	√^b^	√
INTERVENTIONS			
Brief physical activity counseling	√		
Wearable physical activity monitor	√	√	√
Group exercise sessions		√	

^a^in a subset of patients recruited at start of study

^b^assessed continually during the study in G2

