## Statistical analysis

### Sample size justification

The study is powered on between-arm differences in the proportion achieving the primary outcome, minutes per week of moderate-level PA. Our sample size estimation is guided by PA counseling and referral review studies report an effect size between 0.09 and 0.71 for achieving PA guidelines [54–58]. We used the formula given in Vierron and Giraudeau [59] and Vittinghoff and Fitzmaurice [60] with an adjustment for the intraclass correlation coefficient (ICC), where N is the total sample size, the Z’s are the critical value for type I (α = .05) and type II (β = .2) error, σ^2 is the variance in outcome, ρ is the ICC, and π is the proportion (50%) of the N persons assigned to the treatment group. Based on the above formula, assuming an ICC of 0.5 [61], our total sample size of 98 will provide 89% power to detect a 100 min/week of moderate PA difference between groups, corresponding to an effect size of 0.46. Considering an estimated 30% loss to long-term follow-up as reported in similar exercise intervention trials [62], our plan to enroll 98 participants should provide adequate power (80%) to detect differences across intervention arms. Data gathered from those who withdraw from the study will not be used for statistical analyses. This has been accounted for when completing the power analysis, with an additional 20% added to the target sample size. Attrition may be for a number of reasons, which will be ascertained upon withdrawal where possible.

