#### Data analysis

Principal Investigators (Stanford University and Emory University) will be given access to the cleaned data sets. Project data sets will be housed on the REDCap hosted by the respective universities and all data sets will be password protected. To ensure confidentiality, data dispersed to project team members will be blinded of any identifying participant information.

Between-group differences in primary and secondary outcomes will be assessed at 8 and 16 weeks. We will test for differences in primary and secondary outcomes to assess treatment effects using multivariate regression models adjusting for baseline characteristics. We will use mixed-effects linear and logistic regression models to predict changes in continuous PA levels and probability of achieving PA recommendations by regressing study arm, study centers, and an interaction between study arm*centers. The mixed model will include one random effect term accounting for the correlation within study center. Analysis of effectiveness will be according to an intention-to-treat analysis including all enrolled and randomized persons into our analysis. Irrespective of compliance with treatment, all participants will be encouraged to continue with the scheduled outcome evaluation until the end of the study. However, as high as up to 30% loss to long-term follow-up would be expected. The characteristics for those participants without complete follow-up will be examined. If missing data is determined to be random, we will perform a sensitivity analysis using multiple imputation-based methods. If missing observations cannot be assumed to be random, pattern mixture models will be considered [64].

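### Neither the power calculation nor the stated model allows for correlation within the group 2 exercise classes of 8; if outcomes correlate within class, the standard error is too small

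*Protocol article*

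**What the plan says.** The Randomization section allocates individual participants, in blocks of 16. Both groups receive counselling and a wearable. Only group 2 is also referred to twice-weekly classes over the 8-week core period: "Program sessions (8 persons per group) will be specifically designed for persons with CKD". The same section makes the class part of the mechanism: "The social dynamics of the group will be used to forge strong, sustainable relationships with participants", with the weekly activity minutes as the aim.

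The Sample size justification works with "type I (α = .05) and type II (β = .2) error" and 1:1 allocation, and states that "our total sample size of 98 will provide 89% power to detect a 100 min/week of moderate PA difference between groups". It equates this difference with a standardised effect of 0.46 and reaches the figure by "assuming an ICC of 0.5". It does not name the level to which that ICC belongs.

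The Data analysis section lists arm, centre and their interaction as regressors and then says: "The mixed model will include one random effect term accounting for the correlation within study center". Neither class nor instructor appears in the model or in the power calculation. The primary comparison, under Expected outcome, is the change in activity minutes at 16 weeks.

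**The concern.** This is individual randomisation with group delivery in one arm only. With 48 or 49 people in group 2 (the abstract gives a total of 96, the sample size section 98), classes of 8 make about six classes, or about three per site if the sites recruit equally. People who share sessions, a timetable and peers may end up more alike than people who do not, and the protocol intends the group to have this influence. Group 1 has no such classes.

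A model whose only random effect is for centre treats members of a class as independent once arm, centre and arm-by-centre are accounted for. Variation among classes within a site is then counted as if it averaged out over some 48 people, when it averages out over only about six classes. The consequences would be a standard error that is too small, a confidence interval that is too narrow, and a stated power that is too favourable.

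This is not a detail left open for an analysis plan. The protocol states how many random effects there are and at what level.

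**Working it through.** **Inputs**
- From the Sample size justification: alpha 0.05 (sidedness not stated; two-sided reproduces the stated power); N = 98, so n = 49 per arm, since "π is the proportion (50%) of the N persons assigned to the treatment group"; effect size d = 0.46; ICC 0.5; 30% loss.
- From the Group-based physical activity program section: class size m = 8.
- Derived: 49/8 gives about six classes. With 30% loss spread evenly, m = 8 × 0.7 = 5.6 and n = 49 × 0.7 = 34.3.
- Assumed: the class ICC, written ρ. The documents give no value, so a range is shown.

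**1. Reproduce the stated 89%, and see what the ICC of 0.5 does**

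Power = Φ( (d/√f) × √(n/2) − 1.96 ), where f is the factor applied to the variance.
- f = 1 − 0.5 = 0.5: 0.46/0.7071 = 0.6505; × √24.5 = 4.950 gives 3.220; minus 1.960 gives 1.260; Φ = 89.6% (89.0% with the noncentral t).
- f = 1 (no ICC): 62.4%.
- ICC of 0.5 as class clustering in group 2 only, f = (1 + [1 + 7 × 0.5])/2 = 2.75: 27.9%.
- The same clustering in both arms, f = 4.5: 18.8%.

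Of these readings, only the first gives 89%. The ICC therefore enters as a variance reduction and is not an allowance for class clustering.

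**2. Variance of the arm difference with classes in group 2 only**

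Var = (σ²/n) × [1 + 1 + (m − 1)ρ] = (2σ²/n) × v, with v = 1 + (m − 1)ρ/2.
- Full classes: v = 1 + 3.5ρ.
- After 30% loss: v = 1 + 2.3ρ.

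**3. True two-sided type I error when v is ignored**

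Type I error = 2 × [1 − Φ(1.96/√v)].

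| Assumed ρ | v, full classes | Type I error | v, 30% loss | Type I error |
|---|---|---|---|---|
| 0 | 1.000 | 5.0% | 1.000 | 5.0% |
| 0.02 | 1.070 | 5.8% | 1.046 | 5.5% |
| 0.05 | 1.175 | 7.1% | 1.115 | 6.3% |
| 0.10 | 1.350 | 9.2% | 1.230 | 7.7% |

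A simulation agrees: 100,000 runs, 96 participants, six classes of 8, two centres, a model with arm, centre and arm-by-centre, and centre fitted as fixed. It gave 4.9%, 5.8%, 7.1% and 9.4% at ρ = 0, 0.02, 0.05 and 0.10.

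**4. Power when class is allowed for**

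Keep the protocol's own variance factor of 0.5 and apply ρ to the remaining variance: Power = Φ(3.220/√v − 1.96) at N = 98 before dropout.
- ρ = 0.05: 3.220/1.084 = 2.971; minus 1.960 gives 1.011; 84.4%.
- ρ = 0.10: 3.220/1.162 = 2.771; minus 1.960 gives 0.811; 79.1%.

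The analysed N needed for 80% power is 76 at ρ = 0, 88 at 0.05 and 102 at 0.10. These are normal approximations. Degrees of freedom based on about six classes would lower power somewhat further.

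**The case against.** **The error need not exceed 5%.** A reader might infer that the planned test is certain to be anti-conservative. The documents do not support that: it needs a positive class ICC, and none is given. At zero the error is 5.0%, and at 0.02 the excess is under one percentage point. Group 2 is only referred to classes, so attendance may be low. The primary time point falls eight weeks after the core classes end. Either could weaken the correlation. This stands, and the conclusion is conditional for that reason. On the other side, the protocol hopes the relationships will last, and it also tests at 8 weeks, straight after the classes.

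**The false-positive framing is narrow.** If classes changed nobody's activity, treatment could not create class correlation. A positive ICC with a zero mean effect needs some classes to help and others to harm. This is fair: the more realistic harm is an interval that is too narrow when the classes do work.

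**Delivery is not fully described.** Nothing says that each class has its own instructor or fixed membership, and the same type of professional counsels both arms. The arm-by-centre term would capture differences in delivery between sites. All of this is correct, but it leaves variation among classes within a site unmodelled.

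**Two further inferences fail.** The ICC of 0.5 could be taken as the class allowance, but the stated 89% is not reproduced on that reading. It could also be inferred that the 8- and 16-week values enter one model without a participant effect, which would inflate the error further. The protocol says only that differences are assessed at both times and does not describe such a model.

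**Conclusion.** The omission is established in both the power calculation and the stated model. Its consequence depends on a class ICC that the documents do not supply. At plausible assumed values the inflation is modest but real: about 6.3% to 7.1% at 0.05 and 7.7% to 9.2% at 0.10, against a nominal 5%, with the lower figure of each pair reflecting the protocol's own 30% loss. At 0.02 it is hardly visible. The 89% power becomes about 84% or 79% at ICCs of 0.05 and 0.10, before dropout. These figures assume about six classes with stable membership, loss spread evenly over classes, and a two-sided test. The point should be corrected, because the protocol itself gives the reason to expect correlation and the remedy is inexpensive.

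**What to change.** - **Data collection:** record a class identifier for every group 2 participant, defined by the class to which he or she was assigned whether or not sessions were attended, so that it fits the intention-to-treat analysis. Recruitment has begun, and class membership may be hard to reconstruct later.
- **Model:** in the Data analysis section, keep arm, centre and arm-by-centre as fixed effects. Replace the centre random effect with a random class effect in group 2 only, each group 1 participant counting as his or her own cluster (a partially nested model). Use Satterthwaite or Kenward-Roger degrees of freedom. State in advance what is reported if the class variance is estimated as zero. Little is lost by dropping the centre random effect, since there are two centres and centre is already a regressor.
- **Power:** in the Sample size justification, say what the ICC of 0.5 refers to, and restate power with an assumed class ICC and a range around it.

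The cost is one recorded variable and a few sentences. The interval will be wider and the stated power less favourable. The class variance will rest on only about six classes, so it will be imprecise.
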